### Data management, monitoring, and safety reporting

Patient data will be recorded on case report forms (CRFs) built into a REDCap (Research Electronic Data Capture) dictionary hosted at the Neurological Institute of New York, Columbia University. REDCap is a secure, web-based application designed to support data capture for research studies. Participants will be assigned a unique code identification number and all data will be completely anonymized for purpose of analysis and reporting. Electronic data and hard copies will be stored securely.

Data will also be monitored for quality and completeness. Investigators will do their utmost to ensure data completeness, and any missing data will be chased unless confirmed not to be available at the time of each patient close-out visit. Survey data will be directly collected from participants, and thus will not be subject to data verification. All consent forms will be encrypted and stored securely in the Neurological Institute. Any unexpected adverse effects will be reviewed by the primary investigator and reported to the sponsor and ethics committee.

### Data integration

Patient-reported outcomes (PROs) such as post-stroke depressive symptoms and cognitive function will be captured through web-based tablet-enabled software provided by Patient Reported Outcome Measurement Information System (PROMIS), developed by National Institutes of Health funded endeavors to provide precise and flexible electronically administrable tools. Surveys would also be uploaded to the tablet included in the RPBM kit for patients to complete and send automatically from the tablet. RBPM data and online surveys will be collected on a web-based platform and transferred in configured format to integrate into REDCap as patients complete the study. Telehealth visit data will be collected from electronic medical records. The video platform utilized will be noted, to ensure that only currently available HIPAA compliant applications are used.

### Statistical analysis

As this is a feasibility study with a small sample size, pilot data will be used to assess feasibility of the intervention and estimate the variability in the endpoint, while provide preliminary evidence for BP control. A subsequent trial designed will be powered to detect the clinically significant difference to plan a larger confirmatory trial. However, more importantly, descriptive statistics will characterize the randomized patients completing surveys and outcome assessments. Generalized linear modeling will evaluate systolic BP outcome 90 days post discharge as a function of treatment, race/ethnicity, and the interaction of treatment arm and race/ethnicity. We will explore moderating effects of race/ethnicity as secondary analysis. Decisions regarding the pursuit of a subsequent trial will be based on feasibility of the trial, and analysis of all other measures will be hypothesis generating.

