**Methods:**

In this pilot trial, 50 acute stroke patients with hypertension will be screened for inclusion prior to hospital discharge and randomized to usual care or TASC. Usual care patients will be seen by a primary care nurse practitioner at 1–2 weeks and a stroke neurologist at 1 and 3 months. In addition to these usual care visits, TASC intervention patients will see a pharmacist at 4 and 8 weeks and will be enrolled in RBPM consisting of home BP monitoring with interval calls by a centralized team of telehealth nurses. As part of RBPM, TASC patients will be provided with a home BP monitoring device and electronic tablet that wirelessly transmits home BP data to the electronic health record. They will also receive tailored BP infographics that help explain their BP readings. The primary outcome will be feasibility including recruitment, adherence to at least one video visit and retention rates. The clinical outcome for consideration in a subsequent trial will be within-patient change in BP from baseline to 3 months after discharge. Secondary outcomes will be medication adherence self-efficacy and satisfaction with post-stroke telehealth, both measured at 3 months. Additional patient reported outcomes will include depression, cognitive function, and socioeconomic determinants. Multidisciplinary team competency and fidelity measures will also be assessed.

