## Methods

### Study design and overview

This is a parallel two-armed feasibility randomized controlled trial comparing Telehealth After Stroke Care (TASC) intervention (multidisciplinary team care inclusive of pharmacists with home BP monitoring with centralized remote nursing call support and tailored infographics to facilitate understanding of BP data) with usual care. It aims to evaluate the feasibility of a telehealth-based model providing multidisciplinary access including nursing, pharmacy, and physician care, and assess feasibility of an integrated telehealth approach to blood pressure management after stroke. The outcome of BP control will be defined by change in mean awake systolic blood pressure from baseline at the time of discharge through remote monitoring at 3 months.

Remote BP monitoring will be provided with communication through tailored electronic tablet devices with feedback to centralized nurses for tailored telephone-based counseling and communication to providers as needed for elevated readings (Fig. 2).

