**Fig. 2 Fig2:**
[figure not shown]
Remote BP patient monitoring overview of system workflow

We will randomize 25 patients to the TASC intervention, including remote blood pressure monitoring, and 25 patients to usual care. Feasibility measures of interdisciplinary team competency, recruitment, retention, fidelity of implementation, and telehealth patient satisfaction surveys will be assessed in the intervention arm.

To our knowledge, no studies providing accessible integrated care including telehealth and remote BP monitoring with multidisciplinary teams including pharmacy and nursing have been conducted. Such an intervention may reduce racial disparities in post-stroke BP control by providing access to care and facilitating self-efficacy to improve health outcomes.

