### Implementation and future application

The benefits of this study include identifying efficient and effective post stroke care systems, improving access to meaningful care, reducing the risk of recurrent stroke, and promoting patient-centered care. Feasibility of the intervention will be assessed to identify barriers and enablers to complete multidisciplinary telehealth visits and remote monitoring. Key potential problems are difficulties with recruitment and non-return of participants. Barriers to follow up will be addressed by appointment coordination and reminders, as well as coverage of travel costs if needed. If intervention arm participants have technical difficulties, staff will have capacity to make a home visit.

Pilot data collected will also enable our collaborative multidisciplinary team to refine the intervention. Data collected will eventually serve as feasibility data for subsequent study with a primary outcome of within-patient change in systolic BP, and for further peer-to-peer community-based interventions advancing health information.

An additional long-term aim of this project is to develop a long-standing collaboration among researchers in neurology, pharmacy, nursing, epidemiology, and biostatistics to develop additional studies that explore the intersection of community health in our disparate population. It will also allow us to explore successful clinical trial methodology for further implementation in current health systems.

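### The blood pressure model leaves out baseline systolic BP and does not settle whether the response is the 90-day level or the change from discharge

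*Protocol article*

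**What the plan says.** Three places in the protocol article describe the BP outcome as a change:

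- Abstract, Methods: "within-patient change in BP from baseline to 3 months after discharge".
- Study design and overview: "change in mean awake systolic blood pressure from baseline at the time of discharge through remote monitoring at 3 months".
- Implementation and future application, looking ahead to a "subsequent study with a primary outcome of within-patient change in systolic BP".

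The only BP model is in Statistical analysis: "Generalized linear modeling will evaluate systolic BP outcome 90 days post discharge as a function of treatment". Its terms are written out in full: "as a function of treatment, race/ethnicity, and the interaction of treatment arm and race/ethnicity". Baseline systolic BP is neither a covariate nor explicitly subtracted.

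The same section says the pilot data are to "estimate the variability in the endpoint, while provide preliminary evidence for BP control". It also says that the decision on a further trial rests on feasibility and that "analysis of all other measures will be hypothesis generating".

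On design, "We will randomize 25 patients to the TASC intervention, including remote blood pressure monitoring, and 25 patients to usual care". Randomization and blinding stratifies by race and by nothing else.

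**The concern.** The outcome is defined as a change in three places, but the model sentence reads most naturally as a 90-day level. No baseline term links the two.

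With 25 patients per arm and no stratification on BP, the arms can differ noticeably at baseline by chance. A model without baseline BP cannot separate that difference from the treatment effect. It also leaves in the residual the part of the variation that discharge BP would explain.

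At stake are the accuracy of the one BP effect estimate that the pilot will report, and the clarity of the variability estimate that it is meant to pass to the next trial.

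**Working it through.** The document gives no SD, correlation, target difference or power for BP, so there is no BP figure to reproduce. Its only power statement concerns adherence to video visits and is not affected by this point.

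**Inputs.** From the document: 25 per arm, and a retention target of at least 70%, which is 0.7 × 25 = 17.5, or about 18 per arm. Assumed: systolic SD of 18 to 20 mmHg, equal at both times, and a discharge-to-3-month correlation rho of 0.2 to 0.6.

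**Step 1: size of the chance baseline difference.** SE = SD × √(2/n).

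- SD 18, n = 25: 18 × √(2/25) = 5.09 mmHg.
- SD 20, n = 25: 20 × √(2/25) = 5.66 mmHg.
- SD 20, n = 18: 20 × √(2/18) = 6.67 mmHg.

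At SD 20 the difference exceeds 5 mmHg in either direction in about 38% of trials with 25 per arm, and in about 45% with 18 per arm.

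**Step 2: how much enters the estimate.** Given a baseline difference D between arms, the expected shift is rho × D for the level and (rho − 1) × D for the change. Baseline adjustment (ANCOVA) removes it. For D = 5 mmHg:

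| rho | level | change |
|---|---|---|
| 0.2 | +1.0 | −4.0 |
| 0.3 | +1.5 | −3.5 |
| 0.5 | +2.5 | −2.5 |
| 0.6 | +3.0 | −2.0 |

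**Step 3: precision.** Relative to the level comparison, the variance factor is 2(1 − rho) for a change score. For ANCOVA it is (1 − rho²) × [1 + 1/(2n − 4)], where the bracket is the cost of estimating the slope. With n = 25 the bracket is 1 + 1/46 = 1.022. Standard errors use SD 20.

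| rho | SE level | SE change | SE ANCOVA | ANCOVA/level variance | reduction |
|---|---|---|---|---|---|
| 0.2 | 5.66 | 7.16 | 5.60 | 0.981 | 2% |
| 0.3 | 5.66 | 6.69 | 5.45 | 0.930 | 7% |
| 0.5 | 5.66 | 5.66 | 4.95 | 0.766 | 23% |
| 0.6 | 5.66 | 5.06 | 4.57 | 0.654 | 35% |

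The reductions do not depend on the SD. A plain change score is less precise than the level whenever rho is below 0.5, so switching the response to change would not be a remedy by itself.

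**Step 4: simulation check.** In 10,000 simulated trials with 25 per arm, SD 20 and rho 0.5, the empirical SEs were 5.69 (level), 5.61 (change) and 4.97 (ANCOVA). The correlation of the estimate with the baseline difference was 0.51, −0.49 and 0.01 respectively.

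**Step 5: level and change agree once baseline is in the model.** If Y = a + τT + βB + e, subtracting B gives Y − B = a + τT + (β − 1)B + e. The coefficient τ is the same in both, so the choice of response no longer affects the treatment estimate.

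**The case against.** The strongest reply has four parts.

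- **The wording may not conflict.** A reader might infer that the plan contradicts itself by defining a change and analysing a level. The text does not establish that. The outcome in the model sentence can be read as the change already defined in Study design and overview, assessed at 90 days. This stands, which is why the point is an unclear response plus a missing covariate. The missing covariate remains under both readings.
- **The next trial need not be mis-sized.** A reader might infer that it would be planned on the wrong SD. The article does not say that the variability estimate is the regression's residual SD, and the SD of change can be computed directly from the paired readings whatever model is fitted. This stands. What remains is that the article does not say which SD will be reported.
- **The stakes are limited.** Under randomization the unadjusted comparison is unbiased on average and its standard error already allows for chance imbalance. No BP test drives the decision to proceed. This stands and limits the severity. It does not remove the conditional shift in the single trial that will be run.
- **The gain may be small.** Baseline is taken at discharge and follow-up by home monitoring, so a low correlation is plausible. At rho 0.2 the variance reduction is only 2%. This stands for the level reading. Under the change reading a low rho makes the unadjusted analysis worse.

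It might also be said that covariates belong in an analysis plan. Here, however, the model terms are written out, so this is a stated choice.

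**Conclusion.** The point holds as a moderate one. The stated BP model omits baseline systolic BP and leaves open whether the response is the 90-day level or the change from discharge. Under either reading, chance baseline imbalance enters the estimate and precision is lost.

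With an assumed SD of 18 to 20 mmHg, the standard error of that imbalance is about 5.1 to 5.7 mmHg with 25 per arm. The precision available from adjustment, against the level comparison, runs from about 2% of the variance at rho 0.2 to about 35% at rho 0.6. Both SD and rho are assumptions.

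Two further inferences go too far. The analysis is not systematically biased. Nor should the shifts be measured against 5 mmHg as the trial's target difference: the Background links a reduction of that size to lower recurrence risk, but the article sets no target difference for BP.

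**What to change.** In Statistical analysis:

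1. Add discharge systolic BP as a covariate to the model that estimates the treatment effect, with race/ethnicity (the stratification factor) as a main effect.
2. Name the response, and state that with baseline in the model the treatment estimate is the same for the 90-day level and for change.
3. Keep the treatment-by-race/ethnicity interaction, with baseline added, as the secondary moderation analysis that the section already plans. It reflects the trial's focus on disparities and should not be lost in the edit.
4. Report the adjusted difference with its 95% CI. For planning the next trial, also report the SD of within-patient change, the ANCOVA residual SD and the baseline-to-follow-up correlation.

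The cost is one degree of freedom. No new data are needed, because the change outcome already requires the discharge reading.

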## Discussion

Improvement in acute care treatments and prevention have led to decreased mortality among stroke survivors, taking stroke from the third to the fifth leading cause of death in the USA. Moreover, between 2010 and 2030, stroke is projected to have the largest relative increase in total direct medical costs of 238% reaching $95.6 billion and total indirect medical costs of 73% reaching $44.4 billion in the USA [69]. About one-half of patients who survive a stroke are at increased risk of recurrent stroke within a few days or weeks of the initial event, with the greatest risk during the first week [70]. In terms of health care utilization, readmission hospitalizations cost greater than $17 trillion dollars for Medicare [71] and result in hospital penalties. Readmission rates from national data sets suggest up to 21% to occur within the first 30 days after a stroke, with about 1 out of 8 readmissions being considered preventable [72, 73]. The post-acute stroke period offers a valuable target for focused attention to improve patient-centered outcomes.

This pilot study will serve to promote our understanding of the gaps in our population for post stroke care. These data will help us to determine the feasibility of the TASC approach and collect preliminary data for further studies to develop effective telehealth based post-stroke systems of care. Cost-effectiveness analysis of TASC approach will help us understand health care utilization and will also provide insight for a sustainable secondary stroke prevention framework while addressing health disparities.

If feasibility of the TASC multidisciplinary is established, an adequately powered efficacy trial will be planned with goal to study cost-effectiveness of this approach in addition to adequate BP control with enhancement in self-management. In terms of BP telemonitoring, value-based purchasing of equipment may support team-based support. Hospitals may be incentivized with cost savings due to decreased hospital readmissions that are not reimbursed by public insurance. Further, downstream revenue generation in terms of referrals and appropriate testing can also be assessed. These resources can be utilized back among those with limited access to care to selectively provide support among targeted highest risk groups.

### Implementation and future application

The benefits of this study include identifying efficient and effective post stroke care systems, improving access to meaningful care, reducing the risk of recurrent stroke, and promoting patient-centered care. Feasibility of the intervention will be assessed to identify barriers and enablers to complete multidisciplinary telehealth visits and remote monitoring. Key potential problems are difficulties with recruitment and non-return of participants. Barriers to follow up will be addressed by appointment coordination and reminders, as well as coverage of travel costs if needed. If intervention arm participants have technical difficulties, staff will have capacity to make a home visit.

Pilot data collected will also enable our collaborative multidisciplinary team to refine the intervention. Data collected will eventually serve as feasibility data for subsequent study with a primary outcome of within-patient change in systolic BP, and for further peer-to-peer community-based interventions advancing health information.

An additional long-term aim of this project is to develop a long-standing collaboration among researchers in neurology, pharmacy, nursing, epidemiology, and biostatistics to develop additional studies that explore the intersection of community health in our disparate population. It will also allow us to explore successful clinical trial methodology for further implementation in current health systems.

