##### Remote BP monitoring

Our integrated care includes remote BP monitoring and electronic tablet devices provided through New York Presbyterian at no charge to patients with remote support including centralized telehealth nursing calls to patients for elevated readings and driven by patient feedback for frequency.

Patients randomized to telehealth services will be set up with a Philips Remote Blood Pressure Monitoring (RBPM) kit including an electronic device (Samsung tablet with 2-way video capable of telemedicine) and BP/pulse monitor and set up for remote monitoring. These services are designed to reduce disparities in technology literacy with home or remote installation as needed along with step-by-step instructions and explanations provided to each participant in their language of preference. Further, there is no need for patients to have their own technology or internet services as a tablet is included with data transfer capability. BP devices provided have been validated and calibrated for home use.

Certified nurses will touch base through phone calls with patients at intervals set to patient preference and escalate severely elevated BP readings to providers (Fig. 2). BP monitoring results as well as patient reported surveys completed on the electronic tablet are wirelessly transmitted to electronic health records and to a web-based platform (eCare Coordinator) available for the telehealth nurses and the patient’s treating clinical team to see. Critical BP or pulse readings will be shared via system alerts, at which point the call center nurse will contact the patient and assess. If unable, this is to be followed with escalation calls for elevated readings that require immediate attention to the TASC team for resolution (Fig. 2). If patients fail to measure BP data at home for a week that the device automatically transmits, they will be contacted by the call center nurse to enquire. If device trouble shooting is needed, technical assistance will be provided in person or remotely as indicated.

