### Study measures

Feasibility for the project will be monitored with metrics of at least one subject per week to be recruited, weekly and monthly recruitment rates assessed with estimates of these rates gathered at the end of the study. We will assess feasibility of randomization with expected targets of at least 70% of all eligible patients recruited during the enrollment period. We will also assess adherence and retention rates, with expected adherence of at least 70% to at least one video visit in each arm, and retention rates of at least 70% at study completion as stop-go criteria.

Since this is a pilot feasibility study, a sample size calculation was not performed. It is felt that *n* = 50 will be a large enough sample to inform about the practicalities of intervention delivery among patients returning home after an acute stroke. Specifically, with *n* = 25, there is about 85% power at 5% significance (one-sided) to demonstrate an adherence rate of 75% in an arm against a null rate of 50%. We note that in COMPASS-TC study [46] only 35% attended a clinic visit. Therefore, setting the null rate at 50% is reasonable.

Fidelity of implementation will be assessed using a brief checklist at each patient visit by each discipline. An internally designed and validated survey, Telemedicine Satisfaction and Usefulness Questionnaire (TSUQ) [65] provides measures of patient satisfaction and will be collected at 3 months among intervention patients to assess patient satisfaction with telehealth (Table 4). Self-Assessment of Interdisciplinary Research Competencies will be surveyed at the beginning and end of the project to establish progress and satisfaction among TASC providers and investigators in this collaboration [66–68].

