### Data collection

Patient demographics, social determinants of health (age, education, race/ethnicity, address, income, insurance type, along with food, housing, and income security), internet and electronic devices access questions, and medical characteristics (risk factors, comorbidity burden, stroke adjudication) will be collected from the patient and electronic medical records in a data collection form at discharge and at 3 months.

RBPM will be set up for the intervention arm through to 3 months. Patients in the usual care arm will receive the BP monitoring kit with remote assistance at 11 weeks and provide readings at 3 months for outcome assessment. They will also be aided through the remote monitoring team with survey completion if needed. All completed surveys and BP readings will be converted to transferrable format and transmitted via the online platform to REDCap database at 3 months for study completion. Electronic medical records will also be revisited at study end for any additional surveys conducted during patient visits for clinical screening and management purposes.

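### Support for the home BP device that supplies the 3-month outcome differs by arm as written, so 3-month BP may be missing more often in usual care

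*Protocol article*

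**What the plan says.** The BP outcome is defined under Study design and overview as "change in mean awake systolic blood pressure from baseline at the time of discharge through remote monitoring at 3 months". A working, transmitting kit is therefore needed in both arms.

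For TASC, the Remote BP monitoring section offers installation at home or remotely. It adds "If device trouble shooting is needed, technical assistance will be provided in person or remotely as indicated", and on silence from the device: "If patients fail to measure BP data at home for a week that the device automatically transmits, they will be contacted". Implementation and future application then adds "If intervention arm participants have technical difficulties, staff will have capacity to make a home visit".

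For usual care, Data collection states: "Patients in the usual care arm will receive the BP monitoring kit with remote assistance at 11 weeks". Readings follow at 3 months, and Study measures limits them to the first 24 hours. The only further help named for these patients is with completing surveys.

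Some provisions name no arm. Missing data are to be chased up to the close-out visit (Data management, monitoring, and safety reporting). Reminders, appointment coordination and travel costs are offered (Implementation and future application).

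**The concern.** The arms differ in how the outcome is obtained, not only in the treatment tested. A TASC patient whose device fails has about three months and in-person help to put it right. A usual care patient has a short run-in to a 24-hour window and, as written, remote help only. If some controls cannot get the kit working in that time, their 3-month BP is lost for a reason tied to the arm. If those patients also differ in BP, the observed control mean is shifted.

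The pilot is meant to estimate the variability of the BP endpoint (Statistical analysis) and to feed a later trial whose primary outcome is within-patient change in systolic BP (Implementation and future application). Whether BP can be captured equally well in both arms is part of what the pilot should show.

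**Working it through.** The plan gives no figure for BP missingness, so there is none to reproduce on this point. Its only power figure (about 85%, for video-visit adherence) does not bear on BP capture.

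**1. Support side by side**

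| Device support | TASC | Usual care |
|---|---|---|
| When the kit is set up | Discharge | 11 weeks |
| Installation | Home or remote | Remote assistance |
| Troubleshooting | In person or remote | None stated beyond remote assistance |
| Call if no readings | After one week | None stated |
| Home visit for technical difficulties | Yes, arm named | Not stated |
| Period read | Discharge to 3 months | First 24 hours at 3 months |

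Only the home visit is restricted in words. For the other entries the restriction is inferred from their place in the intervention section.

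**2. Time available to controls**

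The kit arrives at 11 weeks: 11 × 7 = day 77. Three months is either the 12-week visit (Telehealth visits by each discipline; 12 × 7 = day 84) or 90 days (Statistical analysis).

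- Time from kit to endpoint: 84 − 77 = 7 days, or 90 − 77 = 13 days.
- If the one-week call also applied to controls, it would fall on day 77 + 7 = 84. That leaves 0 days or 90 − 84 = 6 days.
- A contact at 48 hours would fall on day 79. That leaves 84 − 79 = 5 days or 90 − 79 = 11 days.

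**3. Precision, on assumed missingness**

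The planned size is 25 per arm ("We will randomize 25 patients to the TASC intervention, including remote blood pressure monitoring, and 25 patients to usual care"). All missing fractions are assumptions. The ratio of the standard error of the BP difference to that with full data is √[(1/n_T + 1/n_C) / (2/25)].

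| Missing TASC / usual care | n_T / n_C | SE ratio | Overall completeness |
|---|---|---|---|
| 10% / 10% | 22.5 / 22.5 | 1.054 | 90% |
| 10% / 20% | 22.5 / 20 | 1.087 | 85% |
| 10% / 30% | 22.5 / 17.5 | 1.127 | 80% |
| 10% / 40% | 22.5 / 15 | 1.179 | 75% |

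The formula is symmetric, so the cost is the same if TASC is the arm with more loss. In the last row overall completeness is 75% while usual care stands at 60%, so a pooled figure hides the difference.

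**4. Bias, on assumed selection**

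If a fraction m of controls is missing and the missing differ from the observed by d, the observed control mean is off by m × d.

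- m = 20%, d from 0 to 1 SD: 0 to 0.2 SD.
- m = 40%, d from 0 to 1 SD: 0 to 0.4 SD.
- At an assumed SD of 20 mmHg these are 0 to 4 and 0 to 8 mmHg.

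The bias is zero if missingness is unrelated to BP, and its sign follows the sign of d. The difference d must be taken on the scale analysed: a higher level at 3 months need not mean a smaller change from discharge.

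**The case against.** The strongest reply is that the text does not rule out equal support. The troubleshooting and no-reading sentences name no arm. They stand where the kit is described, and controls receive that kit and deal with the same remote monitoring team. Missing data are chased in both arms, and the kit needs no internet service of the patient's own. TASC patients must keep transmitting for three months and can also stop, so even the direction of any imbalance is uncertain. BP is hypothesis generating, and the decision on a further trial rests on feasibility.

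Much of this stands, and it limits the claim to a risk. It does not remove the asymmetry. The home visit is expressly for one arm, and chasing data cannot recreate a home reading that was never taken.

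A reader might infer more than the documents support:

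- **That controls will lose more readings while TASC loses almost none.** No rate is given for either arm.
- **That loss will concentrate in patients with low technology literacy.** The Background speaks of a potential for wider disparities in use of audio-video technology, and adds that internet access and usability were noted in a majority of stroke survivors.
- **That the control arm would fail the retention criterion.** The text asks for "retention rates of at least 70% at study completion as stop-go criteria" but does not define retention by transmitted BP or set it per arm.
- **That a one-week call always comes too late.** With the endpoint at day 90, six days remain.
- **That the usual care BP measurement at the 3-month follow-up is a ready substitute.** It is described for that arm only and may be the kit reading itself.

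**Conclusion.** The point holds as a risk of differential outcome ascertainment. As written, BP-device support differs by arm, and controls have 7 to 13 days, with remote help only, before a 24-hour reading window. Three-month BP may therefore be missing more often in usual care, and possibly selectively.

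The size and direction of any bias cannot be derived from the documents; the figures above only show what assumed rates would imply. Importance is moderate: no sample size or power statement changes, and BP does not decide whether a further trial follows. It matters for the variability estimate and for the BP outcome carried into that trial, and it is cheap to correct now.

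**What to change.** 1. In Implementation and future application, offer the home visit to participants in either arm for device problems that affect the 3-month reading.
2. In Data collection, apply to controls, when their kit is issued, the set-up and troubleshooting options listed under Remote BP monitoring.
3. Have the existing call-centre nurse contact any control with no transmitted reading within about 48 hours of set-up, rather than after a week. This needs a test transmission at set-up, because the text places control readings at 3 months.
4. Report 3-month BP completeness by arm, with reasons for missing readings.
5. Use a BP taken at a visit only as a flagged sensitivity analysis, and only if a separate reading of that kind exists in both arms.

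The cost is a few words, an earlier call by staff already in place, one completeness table and possibly a few extra home visits by existing staff.
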